### Design and settings

This prospective single-center, participant- and assessor-blinded, randomized controlled trial (RCT) will be conducted in the ICU of Toho University Omori Medical Center, a tertiary emergency care facility affiliated with Toho University in Tokyo, Japan. The ICU comprises both a general ICU and an emergency ICU managed by the institution.

The study protocol has been approved by the Ethics Committee of the Faculty of Medicine at Toho University (approval number: T2024-2411). Written informed consent will be obtained prior to enrollment. For patients who are conscious and able to make decisions, consent will be obtained directly; for those who lack decision-making capacity, consent will instead be sought from family members or legally authorized representatives.

No independent data safety monitoring board was established due to the pragmatic, low-risk nature of the trial. Participant safety will be ensured through routine ICU clinical governance, with continuous monitoring for adverse events related to nutrition therapy and mobilization. Safety data will be reviewed periodically by the principal investigator, and serious adverse events will be reported to the institutional ethics committee in accordance with local requirements. The trial may be suspended or terminated if unexpected safety concerns arise.

### Participants

Patient enrollment will begin on September 30, 2025. Eligible participants will be critically ill adults aged ≥ 18 years who are admitted to either the general ICU or emergency ICU, are independent in activities of daily living prior to admission, and are expected to require mechanical ventilation for at least 48 h. Patients receiving extracorporeal membrane oxygenation (ECMO) will also be included.

Exclusion criteria will include the following: patients admitted for scheduled surgery; those with a body weight ≥ 200 kg, exceeding the device load limit; patients admitted with neuromuscular diseases; those who undergo surgery resulting in lower-limb amputation or weight-bearing restriction after admission; patients transferred from another hospital after more than 48 h of mechanical ventilation; those unable to receive enteral nutrition; and patients with a life expectancy of < 7 days of ICU admission.

Neuromuscular diseases include conditions such as muscular dystrophies, amyotrophic lateral sclerosis, inflammatory or metabolic myopathies, Guillain-Barré syndrome, myasthenia gravis, chronic inflammatory demyelinating polyneuropathy, and other neuromuscular disorders associated with significant motor weakness. These conditions were excluded because disease-specific motor weakness, whether acute or chronic, may substantially affect baseline mobility and responsiveness to rehabilitation, thereby confounding the evaluation of functional recovery using the motor subscale of the Functional Independence Measure (FIM motor score).

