### Interventions

The intervention in this study will not involve differences in the intensity or frequency of rehabilitation; the focus will be on modifying protein intake between the two groups. In the control group, nutritional support will target the lower limit of protein intake recommended in current guidelines (1.2 g/kg/day) [9, 10]. In contrast, participants in the intervention group will receive a higher protein intake of 1.8 g/kg/day. As described previously, both caloric and protein intake will be adjusted to remain within 100–110% of the prescribed targets. Although European Society for Clinical Nutrition and Metabolism guidelines suggest higher protein targets for selected populations, such as trauma or obese patients [9], the present trial is not designed to individualize protein prescription based on diagnostic subgroups, but rather to evaluate the effect of two predefined protein targets under standardized mobilization conditions. Randomization is expected to distribute such patient characteristics evenly between groups.

The core intervention period will continue from Day 3, when protocolized protein delivery is initiated, until ICU discharge, death, or the initiation of oral intake, whichever occurs first, for a maximum of 28 days from randomization. During this period, standardized high-intensity mobilization will be provided as part of routine ICU care to all eligible patients.

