### Sample size estimation

Our previous study was the first to investigate early mobilization of ICU patients using an MPL [22]. However, because the primary outcome in the present study differs, no optimal prior data are available to directly inform the sample size calculation. Therefore, we referred to previous studies on post-stroke patients and adopted a standard deviation (SD) of 20 and a minimal clinically important difference of 17 for the FIM motor score [25].

As there is no established SD or MCID for the FIM motor score at hospital discharge for mechanically ventilated ICU survivors, we used estimates from the post-stroke rehabilitation literature, where FIM is most extensively validated. Variability in ICU survivors may plausibly be larger owing to heterogeneity in diagnoses and ICU-related factors (e.g., sedation, delirium, complications), which could lead to underpowering; however, the direction and magnitude of this difference are uncertain.

The sample size was calculated using Power and Sample Size Calculation software (PS, version 3.1.2, Vanderbilt University, Nashville, TN, USA). With a two-sided *α* of 0.05 and *β* of 0.95, the required sample size was 37 patients per group, yielding a total of 74. To account for an anticipated 15% dropout rate, the final sample size was set at 90 participants.

The feasibility of recruiting 90 participants over ~ 20 months is supported by prior experience from our previous single-center MPL study in the same ICU, in which 92 patients were enrolled within approximately 20 months [22].

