### Data collection

Baseline characteristics will be collected at the start of the intervention, and will include demographic and clinical data: age, sex, body mass index, primary diagnosis, and comorbidities assessed using the Charlson Comorbidity Index [26]. Severity of illness will be measured using the Acute Physiology and Chronic Health Evaluation (APACHE) II score. Additional clinical variables will include the presence of acute kidney injury (AKI) according to the Kidney Disease: Improving Global Outcomes criteria [27], presence of diabetes, score on the Malnutrition Universal Screening Tool [28], and the presence of malnutrition defined by the Global Leadership Initiative on Malnutrition criteria [29]. Furthermore, body composition will be assessed at enrollment using a bioelectrical impedance analyzer (InBody BWA2.0S; InBody Japan, Tokyo, Japan) to determine parameters including skeletal muscle mass, skeletal muscle index, fat-free mass index, and phase angle. Baseline FIM scores will not be collected because most patients are unable to undergo functional assessment at ICU admission due to sedation, mechanical ventilation, or impaired consciousness. Therefore, FIM was assessed only at hospital discharge, consistent with the study objective of evaluating post-ICU functional recovery.

Nutritional data will include the number of days from admission to initiation of enteral nutrition, the number of days until the target protein dose was achieved, and the mean intake of caloric, protein, parenteral caloric, enteral caloric, parenteral amino acid, and enteral protein during the intervention period. These data will be analyzed separately for Days 0–1 and from Day 3 onward.

Rehabilitation-related data will include the number of days from admission to initiation of mobilization, number of days mobilization was performed, and the ICU Mobility Scale score at ICU discharge [30].

In addition, treatment-related data will include the use of renal replacement therapy, use of ECMO, and the duration of mechanical ventilation.

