### Outcome

The primary outcome will be the total motor domain score of FIM at hospital discharge. The FIM motor score at hospital discharge was selected as the primary outcome because it represents the earliest clinically stable time point at which the cumulative effects of ICU-based interventions can be meaningfully assessed. FIM at ICU discharge may be influenced by non-clinical factors such as bed availability and transfer policies, and may underestimate functional recovery due to ongoing critical illness and sedation effects. In contrast, longer-term follow-up after discharge is more susceptible to loss to follow-up and confounding by post-ICU rehabilitation and social factors. Therefore, assessment at hospital discharge was considered the most appropriate balance between clinical relevance, feasibility, and internal validity.

Secondary outcomes and their assessment time points will be as follows:At ICU discharge: Functional Status Score for the ICU [31], Medical Research Council (MRC) score, and ICU length of stay.At 14 days after ICU discharge: FIM motor, cognitive subscale of FIM (FIM cog), Mini-Mental State Examination (MMSE), body composition parameters, MRC score, and Brief Pain Inventory (BPI).At hospital discharge: MRC score, FIM cog, body composition parameters, BPI, length of hospital stay, and mortality.At 60 days after hospital discharge: FIM motor score, MRC score, FIM cog, MMSE score, body composition parameters, and BPI.

Follow-up at 60 days post-discharge will be conducted during an outpatient visit scheduled at the time of discharge. For patients who die or cannot be assessed owing to severe consciousness disturbance, the FIM motor and FIM cog will be recorded at their minimum values (13 and 5, respectively), the MRC score will be assigned as 0, and the BPI will be recorded as missing. For patients who die before hospital discharge, FIM scores will be assigned as the minimum possible values (motor score 13 and cognitive score 5). This approach reflects that death represents the worst possible functional outcome and ensures that mortality is appropriately incorporated into the analysis of functional recovery rather than treated as missing data.

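### The reason given for excluding neuromuscular disease applies equally to acute central lesions, yet these patients stay eligible and the primary FIM motor comparison does not adjust for them

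*Protocol article*

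**What the plan says.** **Eligibility (Participants).** The relevant exclusions are "patients admitted with neuromuscular diseases; those who undergo surgery resulting in lower-limb amputation or weight-bearing restriction after admission". The definition of neuromuscular disease covers muscle, motor-neuron, junction and peripheral-nerve conditions, and its list ends with "Guillain-Barré syndrome, myasthenia gravis, chronic inflammatory demyelinating polyneuropathy, and other neuromuscular disorders associated with significant motor weakness". The catch-all therefore stays within neuromuscular disorders. The reason given is that "disease-specific motor weakness, whether acute or chronic, may substantially affect baseline mobility and responsiveness to rehabilitation, thereby confounding the evaluation of functional recovery", with the FIM motor score named as the measure affected. Eligible patients "are independent in activities of daily living prior to admission, and are expected to require mechanical ventilation for at least 48 h".

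**Allocation (Randomization).** Variable blocks of four, six or eight, 1:1, with no stratification factor stated.

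**Analysis (Statistical analyses; Subgroup analysis).** Outcomes are compared by Student's t-test or Mann–Whitney test under intention to treat. The adjusted sensitivity analyses name exposure durations, AKI and RRT. The subgroups are sex, AKI, RRT, diabetes, two durations and APACHE II. Diagnosis appears in none of these.

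**Data collection.** The baseline record includes "age, sex, body mass index, primary diagnosis, and comorbidities assessed using the Charlson Comorbidity Index". Baseline FIM is not collected.

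**Sample size estimation.** SD 20, difference 17, 37 per group, 90 in total after 15% dropout. The section concedes that "Variability in ICU survivors may plausibly be larger owing to heterogeneity in diagnoses and ICU-related factors", and makes no allowance for it.

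**The concern.** The criterion is narrower than its own justification. By writing acute as well as chronic, and by listing Guillain-Barré syndrome, the protocol shows that it did not regard pre-admission independence as enough protection against new motor weakness. A patient who was independent until an acute stroke, cord injury or brain injury arrives with the same problem and remains eligible. Recruitment includes the emergency ICU of a tertiary emergency facility, so such admissions are plausible, although their number is not stated.

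Two things are at stake. A subgroup with much lower discharge FIM motor scores widens the spread of the primary outcome. If the lesion also prevents the loading on which the trial's hypothesis depends (Background), these patients may respond less to protein and shrink the average effect. With no baseline FIM to absorb prognostic variation, the diagnosis recorded at admission is one of the few baseline variables that could do so, and the planned analyses do not use it.

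**Working it through.** **1. The plan's own figure.** Inputs from Sample size estimation: difference 17, SD 20, two-sided alpha 0.05. The printed beta of 0.95 makes sense only as power, and is read so here. The noncentral t gives 94.5% power at 36 per arm and 95.0% at 37, so 37 per group reproduces. Dropout: 74 / 0.85 = 87.1, or 88 in even arms; 90 is consistent with that.

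**2. Does the omission bias the test?** In a simulation with no treatment effect, a 20% lesion share, a 30-point deficit and 37 per arm, the unadjusted t-test rejected in 4.9% of trials. Type I error is protected.

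**3. Assumptions for the size.** The documents give neither the lesion share q nor the FIM deficit. I take q = 10%, 20%, 30% and SD 20 within each patient type.

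*Scenario A, protein works equally in everyone.* Lesion patients score 30 points lower in both arms. The difference stays 17 and SD = √(20² + q(1−q)·30²). For q = 20%: √(400 + 0.16 × 900) = √544 = 23.3.

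*Scenario B, lesion patients gain nothing.* They average 30 in both arms; the others average 60 versus 77. The difference becomes 17(1−q). The gap is 30 points in the control arm and 47 in the high-protein arm, so the pooled variance is 400 + q(1−q)(30² + 47²)/2. For q = 20%: difference 13.6, SD = √(400 + 0.16 × 1554.5) = √648.7 = 25.5.

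*Scenario B adjusted for the flag.* One common coefficient removes the average gap of 38.5 and leaves ±8.5 in each arm, so the residual variance is 400 + q(1−q)·8.5². For q = 20%: √(400 + 0.16 × 72.25) = 20.3. The difference stays 13.6.

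Power at 37 per arm (noncentral t):

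| q | A: SD | A: power | B: difference | B: SD | B: power | B adjusted: SD | B adjusted: power |
|---|---|---|---|---|---|---|---|
| 10% | 21.9 | 91% | 15.3 | 23.2 | 80% | 20.2 | 90% |
| 20% | 23.3 | 87% | 13.6 | 25.5 | 62% | 20.3 | 81% |
| 30% | 24.3 | 84% | 11.9 | 27.0 | 47% | 20.4 | 70% |

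In scenario A, adjustment brings the residual SD back to 20, so about 95% power is recovered. In scenario B it removes the extra spread but leaves the smaller difference.

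**4. Sensitivity to the assumptions.** With a lesion mean of 40 instead of 30, scenario B gives 84%, 70% and 55%. With all 45 per arm contributing, scenario A gives 95%, 93% and 91%, and scenario B (mean 30) gives 87%, 71% and 54%.

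**The case against.** Several points on the other side stand.

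- **Not biased.** A reader might infer from the protocol's use of the word confounding that the treatment comparison is biased. It is not: allocation is randomized and the test keeps its level. Chance imbalance in lesion patients is also not a separate harm, because it is part of the variance already counted in the power figures.
- **Case-mix unknown.** A reader might take the scoring rule for patients who "cannot be assessed owing to severe consciousness disturbance" (Outcome) as proof that brain-injured patients will be enrolled. The rule names no cause and gives no numbers.
- **The balance sentence is about something else.** "Randomization is expected to distribute such patient characteristics evenly between groups" (Interventions) follows a remark on trauma and obese patients, for whom guidelines suggest higher protein targets. It does not say how the trial handles motor deficit.
- **Other criteria narrow the gap.** Pre-admission independence removes most disabling chronic deficits. The life-expectancy exclusion may remove some severe brain injuries, and the weight-bearing exclusion some spinal injuries.
- **Breadth is a stated aim.** The Discussion values an inclusive cohort, so keeping these patients is defensible.
- **The large losses need a strong assumption.** Zero protein effect in lesion patients is not established by the documents, and the planning SD and difference themselves come from post-stroke patients.

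It can also be said that covariates belong in an analysis plan that is not shown. That holds for detail. But the article does state its primary method, and that method is unadjusted.

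**Conclusion.** The mismatch between criterion and rationale is real, and nothing in the stated allocation or analysis takes it up. The consequence is limited to lost precision and possible dilution in the primary FIM motor comparison.

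The size is hypothetical throughout. For a 10–30% share and a 30-point deficit, power at 37 per arm is 91–84% if the protein effect is the same in everyone. It is 80–47% only if these patients gain nothing, with the means assumed above. Using 45 per arm softens both ranges. A reader might take the lower range as the expected power of this trial, but the documents support neither the share nor the absence of effect.

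The change is worth making because the adjustment costs almost nothing and uses a variable already collected. The documents do not show that these patients must be excluded.

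**What to change.** 1. Keep these patients, and say in Participants why the exclusion stops at neuromuscular disease.
2. Define a yes/no flag for acute central lesion at admission (stroke, spinal-cord injury, traumatic or hypoxic brain injury). Derive it from the primary diagnosis already collected, using admission information only and without knowledge of allocation.
3. Include the flag as a baseline covariate in the primary FIM motor comparison, for example by ANCOVA in place of the unadjusted t-test or Mann–Whitney test.
4. Pre-specify a sensitivity analysis of the FIM motor score without the flagged patients.
5. If randomization can still be changed, also stratify the blocks by the flag.

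**Cost.** One extra baseline field and slightly more analysis work. Stratifying needs an amendment, because recruitment opened on September 30, 2025, although no participant had been enrolled when the article was submitted (Trial status). Items 2 to 4 remain possible before unblinding. Adjustment will not recover any dilution.

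Extending the exclusion is optional. It would match the rationale more closely, at the price of slower recruitment and a less inclusive cohort.

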### Rehabilitation protocol

In this trial, “high-intensity mobilization” is operationally defined as achieving out-of-bed mobilization at the level of standing or higher (e.g., standing or stepping) at an earlier stage of ICU stay than would be feasible with conventional mobilization methods, facilitated by the use of an MPL.

The criteria for initiating and discontinuing rehabilitation will follow those established in our previous studies [22, 23]. The initial rehabilitation level will be determined through discussion among physicians, nurses, and physical therapists (Fig. 1). Rehabilitation sessions will be conducted daily and will follow a stepwise progression, with each session set at a higher intensity than the preceding session (Fig. 2). Following the initial successful achievement of sitting at the edge of the bed, patients will undergo early high-intensity rehabilitation (standing or higher) using a MPL. Our prior research demonstrated that the use of an MPL enables patients to achieve standing earlier than that achieved with standard care [22]. For patients who are capable of standing or higher-level mobilization without MPL support, the device will not be required. Thus, the purpose of this protocol is to create a cohort in which earlier and more intensive rehabilitation can be performed using the MPL. Rehabilitation with MPL will continue until patients are transferred from the ICU to the general ward.

**Fig. 1 Fig1:**
[figure not shown]
ICU rehabilitation initiation and discontinuation criteria. The flowchart summarizes the criteria for initiating and discontinuing ICU rehabilitation.The left panel describes the physiological and safety requirements for rehabilitation initiation, including respiratory, circulatory, and neurological stability, as well as sedation and analgesic evaluation (RASS, NRS, and BPS). The right panel outlines discontinuation criteria such as neurological changes, respiratory or circulatory instability, uncontrolled pain, or device-related risks. When discontinuation criteria are met, rehabilitation should be paused and restarted at a lower intensity level once the patient’s condition stabilizes. Abbreviations: MI, myocardial infarction; BP, blood pressure; SAT, spontaneous awakening trial; SBT, spontaneous breathing trial; RASS, Richmond Agitation-Sedation Scale; NRS, numerical rating scale; BPS, behavioral pain scale

**Fig. 2 Fig2:**
[figure not shown]
Stepwise ICU rehabilitation protocol. The rehabilitation program is divided into five progressive levels. Level 1 consists of MRC muscle strength and ROM exercises. Subsequent levels involve resistance training, heads-up positioning, sitting on the edge of the bed, and standing or walking using a mobile patient lift when necessary. Progression to the next level is permitted if the discontinuation criteria are not met; if the discontinuation criteria are met, rehabilitation is resumed at one level lower. Resistance training should be conducted for areas with an MRC score ≤ 3. Abbreviations: MRC, Medical Research Council; ROM, range of motion

Mobilization is delivered daily, including weekends. On weekdays, mobilization is led by physiotherapists; on weekends, mobilization at the predefined high-intensity level (standing or higher) is maintained by trained ICU nurses (and physicians when needed) using the mobile patient lift, following the same standardized protocol and safety criteria. This approach was used in our previous MPL study [22] and was feasible without a physiotherapist present on weekends. Mobilization will be performed twice daily and, when feasible, up to three times daily. The appropriate number of sessions will be determined through discussion among physicians and nurses, with adjustments made as needed.

In cases where the patient refuses mobilization, the response will depend on the underlying reason. If refusal is due to pain or fever, symptomatic treatment will be provided. If refusal is due to fatigue, the session will be rescheduled. If patients exhibit depressive symptoms and decline participation, staff will provide supportive listening and ensure that no coercion is applied. When clinically indicated, consultation with appropriate specialists (e.g., psychiatry or psychosomatic medicine) will be arranged according to standard clinical practice. However, the patient will be approached again, and if consent is obtained, mobilization will be performed.

The frequency and duration of each mobilization session will be routinely documented in the electronic medical records as part of standard ICU practice and will be extracted for analysis.

